**Fig. 1 Fig1:**
[figure not shown]
Flow chart of the randomization of day-care centres

We will (if possible) arrange blocks of centres that are similar to one another (in terms of region and/or target group: i.e. severity of dementia, age of onset, ethnicity, group size in the day-care centre). This is to control for environmental factors that might possibly influence the outcomes. Within these blocks, day-care centres will be randomized by an independent researcher, using Random Allocation Software [48], to either the experimental (exergaming) group or control (regular activities) group (12 day-care centres per group). After randomization, the day-care centres will remain in the experimental or control group throughout the duration of the trial.

Day-care centres which already have the required exergaming equipment, will be paired up with a comparable day-care centre from the same or another care organization without the equipment. Then they will be randomized as a pair instead of as an individual day-care centre. If this pair is randomized in the experimental group, the day-care centre with the exergaming equipment will participate in the trial. Similarly, if this pair is randomized in the control group, the day-care centre without the equipment will participate in the trial. Day-care centres which do not have any exergaming equipment yet, can also be enrolled for randomization individually if they are willing and able to buy the exergaming equipment needed for the trial. This has to be confirmed, prior to randomization, and is intended to ensure they can still participate when they are randomized to the experimental group.

Day-care centres in both groups will each receive an allowance of at most € 1.125,-. When they recruit eight persons or more. They can decide themselves how they want to spend this, for example to pay their staff for the extra hours they have to put in to participate in the research project. Day-care centres in the experimental group may also put this amount towards the purchase of the exergaming equipment.

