### Sample size calculation

Since a high quality study evaluating the effect of a similar intervention on physical activity and mobility was not available when we were writing our protocol, we used previous results on exergaming regarding one of our secondary outcome measures (memory) for this power calculation [38]. We performed a power analysis based on a power of 80% and a difference of 2 (with a standard deviation of 4.6) between scores on the Mini-Mental State Examination (MMSE) [50]. We chose an Intracluster Correlation Coefficient (ICC) of 0.05. This resulted in a sample size of 166 participating dyads with an alpha of 0.05. When also taking into account the cluster effect of the day-care centres (7 dyads per cluster) and drop out (4%), the total sample size needed is 224 dyads.

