### Outcome measures

#### Primary outcome measures

The primary outcome measures are the physical activity and mobility of the participants with dementia and can be found in Table 1. Physical activities (including exergaming) he/she is engaging in (how many times a week, and for how long) in the day-care centre and at home will be registered using a custom-developed registration form during 1 week at the three measuring moments. With regard to mobility, information will be gathered with a short physical test, the Short Physical Performances Battery (SPPB) [55]. This test consists of three subtests: balance, gait speed, and chair stand and is used to evaluate lower extremity functioning in older adults.

**Table 1 Tab1:** Primary outcome measures for participants living with dementia

Outcome	Outcome measures for participants with dementia	Recorded by	Timing		
			Baseline	3 months	6 months
Mobility	Short Physical Performance Battery (SPPB) [55]	Researcher by means of test with participant with dementia	X	X	X
Physical activities of the participant living with dementia	Custom-developed registration form	Informal caregiver	X	X	X
Physical activities of the participant living with dementia	Custom-developed registration form	Staff at day-care centre	X	X	X

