### Analysis of the data

#### Effect evaluation

Descriptive statistics at baseline will be used to compare participants with dementia, informal caregivers and staff of day-care centres in the experimental group with the control group. This will provide information on the differences between the intervention and control group at the start of the study.

The baseline scores of the people, who drop out of the study will be compared to those, who remain in the study. This will provide information about selective drop-out. Participants, who drop out during the trial will be included in the main analysis by imputing their scores using multiple imputation.

The effectiveness of the intervention will first be examined by comparing percentages, or mean scores (Chi-Square test, Mann-Whitney U test and T-tests (*p* < 0.05). Second, we will use mixed model regression analysis which will take into account the effect of clustering on the level of the day-care canters, confounders and missing data. The regression analysis will be conducted in three steps. Firstly, an analysis will be carried out for the primary and secondary outcome measures. If any differences in variables related to the outcome measures between the experimental group and the control group are found at baseline, these are added as potential confounders to the model for each outcome measure to check whether the uncorrected Beta-coefficient (β) changes with more than 10%, which means that this variable will remain in the model as a confounder. Examples of potential confounders are type of exergaming equipment, amount of support from staff, severity of dementia etc. Finally, mixed model analysis will be conducted for each outcomes variable for both follow up measurements (three and 6 months) with the selected confounders included in the analysis.

The method of QUalitative INteraction Trees (QUINT) [63] will be used for subgroup analysis. This allows for the identification of subgroups for whom the effect of the intervention differs, for example differences related gender, age, ethnicity or severity of dementia. Cut-off values do not need to be defined beforehand. Based on the QUINT analysis, more specific advice can be formulated with regard to which type of participant or informal caregiver the intervention has a positive effect or not.

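### The baseline value of each outcome is not a fixed covariate in the final mixed model; the only stated covariate rule is data-driven and would usually leave it out

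*Protocol article*

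**What the plan says.** The protocol article, Analysis of the data, Effect evaluation, describes a mixed model regression that accounts for clustering by day-care centre, confounders and missing data. It proceeds in three steps.

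1. An analysis of each primary and secondary outcome; its model terms are not listed.
2. Variables related to the outcome on which the arms differ at baseline are tried one model at a time, and kept if the uncorrected coefficient changes by more than 10%. The examples given are equipment type, staff support and dementia severity.
3. Finally, "mixed model analysis will be conducted for each outcomes variable for both follow up measurements (three and 6 months) with the selected confounders included".

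Table 1 schedules the SPPB and both activity registration forms (caregiver and staff) at baseline, 3 and 6 months. Tables 2 to 4 do the same for nearly all secondary scales.

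On design, the section on recruitment and randomisation of centres says that similar centres are grouped into blocks where possible. "Within these blocks, day-care centres will be randomized by an independent researcher", with "12 day-care centres per group". The blocks are not named among the model terms.

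The Sample size calculation uses MMSE, a secondary outcome: "We performed a power analysis based on a power of 80% and a difference of 2 (with a standard deviation of 4.6" between scores. It continues: "We chose an Intracluster Correlation Coefficient (ICC) of 0.05" and "This resulted in a sample size of 166 participating dyads with an alpha of 0.05". The total then allows for "the cluster effect of the day-care centres (7 dyads per cluster) and drop out (4%), the total sample size needed is 224 dyads".

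**The concern.** In a randomised trial the baseline score of an outcome belongs in the model because it predicts the follow-up score. Whether the arms happen to differ on it is a separate matter, and that is the only thing the stated rule looks at. A strongly prognostic baseline score that is well balanced would be left out, and its share of the outcome variance would stay in the error term.

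The rule also makes the set of covariates depend on the data, separately for each outcome. Chance imbalance is corrected in some analyses and not in others, and small changes in the data can move a variable across either threshold. With only 24 randomised units, chance imbalance between arms is likely enough to matter. The baseline measurements are already being collected, so the cost of not using them is avoidable.

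**Working it through.** **Inputs from the documents.** Difference 2, SD 4.6, alpha 0.05, power 80%, ICC 0.05, 7 dyads per cluster, dropout 4%, total 224 (Sample size calculation); 24 centres, 12 per arm. The article does not state whether alpha is one- or two-sided; two-sided is used because it reproduces the plan.

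**Assumed.** The correlation r between baseline and follow-up, shown at 0.3, 0.5 and 0.7. The documents give none.

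**Step 1: reproduce the plan.** Total before clustering = 4 × 4.6² × (1.96 + 0.8416)² / 2² = 166.1, matching 166. Design effect = 1 + (7 − 1) × 0.05 = 1.30, and 166 × 1.30 = 215.8. Then 215.8 / 0.96 = 224.8 (or 215.8 × 1.04 = 224.4), matching 224. No baseline adjustment enters this calculation.

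**Step 2: unadjusted power in the design as laid out.** Analysed dyads: 224 × 0.96 = 215. Per centre: m = 215 / 24 = 8.96.

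SE = √[2 × 4.6² × (0.05 + 0.95 / m) / 12] = 0.742.

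Noncentrality = 2 / 0.742 = 2.70. With a t reference on 24 − 2 = 22 degrees of freedom, power is 73.1%. If all 224 were analysed it would be 74.3%.

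**Step 3: add the baseline value.** There are two cases.

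- *A:* the same r holds at person and centre level, so the whole variance is multiplied by 1 − r².
- *B:* only the within-centre part is reduced, so the bracket becomes 0.05 + 0.95 × (1 − r²) / m.

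| r (assumed) | SE, A | Power, A | SE, B | Power, B |
|---|---|---|---|---|
| 0 | 0.742 | 73.1% | 0.742 | 73.1% |
| 0.3 | 0.708 | 77.1% | 0.719 | 75.8% |
| 0.5 | 0.642 | 84.5% | 0.676 | 80.7% |
| 0.7 | 0.530 | 95.0% | 0.606 | 88.4% |

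**Step 4: how often would the stated rule keep the baseline value?** This was simulated with 24 centres of 9 dyads, ICC 0.05, a true difference of 2, equal r at both levels and 4,000 trials per r. A baseline difference was read as p < 0.05 ignoring clustering, followed by the 10% criterion. The baseline value was kept in 9.7% (r = 0.3), 10.9% (r = 0.5) and 10.6% (r = 0.7) of trials. On that reading, about nine trials in ten would forgo the gain. The article does not define what counts as a difference. A looser reading would keep the variable more often, but the choice would still depend on the data.

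**Step 5: blocks.** Let q be the assumed share of between-centre variance that the blocks explain. On the same base, 73.1% without blocks compares with 69.0%, 72.6% and 76.4% for q = 0, 0.25 and 0.5 if blocks are pairs fitted as fixed effects (11 degrees of freedom). Pairs are an assumption, since the article gives no block size. The effect on power can go either way.

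**The case against.** The strongest reply is that the article never says the baseline score is handled by the two-stage rule. That rule is written for potential confounders, step 1 lists no model terms, and a fuller analysis plan may already fix the baseline value. This stands in part. The article does not exclude baseline adjustment, and a reader who infers a decision against it goes further than the text. What remains is that the one covariate rule the article does state is data-driven, and its final model is described by what that rule selects. Dementia severity is among the candidates, and the inclusion criteria define mild to moderate dementia by MMSE score. Baseline MMSE could therefore plausibly be screened in this way.

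Three stronger readings are tempting and are not supported.

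- *That leaving out adjustment invalidates the stated 80% power.* The planned 224 assumes no adjustment. The 73% in step 2 comes from spreading the dyads over 24 centres at about 9 each, where the plan used 7, and from a t reference. That is a separate sample-size matter.
- *That omitting the blocks is an error.* Blocks are formed only where possible, their size is not given, leaving them out usually makes the test conservative rather than biased, and fixed small blocks can lose power.
- *That the test would exceed its nominal size with so few clusters.* That would need Wald z-tests, and the article specifies no such test.

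It is also fair to object that the figures rest on MMSE. No SD or baseline correlation is given for SPPB or physical activity, so the gain for the primary outcomes cannot be computed from the documents.

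**Conclusion.** The point holds as a matter of how the model is specified. As written, the covariates come from observed imbalance plus a 10% change, and the baseline value of the outcome is not guaranteed a place although it is measured. The likely result is lost precision and inconsistent handling of chance imbalance; the documents do not show bias in the planned analysis or a wrong sample size.

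For MMSE, power would rise from about 73% by 3 to 4 points at r = 0.3, by 8 to 11 at r = 0.5 and by 15 to 22 at r = 0.7. These gains assume 215 analysed dyads, 24 equal centres, ICC 0.05, 22 degrees of freedom and the stated r; the range reflects whether centre-level variance is also reduced. The direction carries over to any outcome whose baseline predicts follow-up, but the size for the primary outcomes is unknown. This should be changed. The block element is only an option.

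**What to change.** For every outcome measured at baseline, state that its baseline value is a covariate in the model for the 3- and 6-month measurements, regardless of any observed difference between arms. Let this replace the baseline-difference and 10% rule, and name any further covariates in advance. Settle the wording before outcomes are compared by arm.

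Optionally, where blocks were actually formed, represent them by a random effect or by their defining factors (region, target group), rather than by fixed effects for very small blocks.

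The cost is analysis wording and one coefficient per model. No new data or participants are needed. Block terms, if used, may cost some degrees of freedom.

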## Discussion

Large and scientifically robust studies to evaluate the effects of exergaming for people living with dementia are lacking. The aim of this study is to evaluate the effectiveness and cost-effectiveness of exergaming for people living with dementia and their informal caregivers. If the exergaming intervention proves to have positive effects, this may boost the uptake of the exergaming intervention in other day-care centres. Implementation will be supported by the findings from our process evaluation, which will provide extensive information on factors that either promote or hinder successful implementation of exergaming for this target group.

We expect that exergaming will have positive effects on people living with dementia in several domains such as physical, cognitive, emotional, and social functioning, and on quality of life for both people living with dementia and their informal caregivers. We hope that the results of this project will motivate people with dementia to exercise more and as a result to experience positive effects on their wellbeing and the quality of life. We envision that this may have a positive effect on the burden of care experienced by their informal caregiver as well. Finally, we expect that societal costs of the people living with dementia and their informal caregivers are affected.

There are several challenges that lie ahead when starting this research project. Recruitment can be a complicated process with several steps that have to be taken. Firstly, day-care centres have to be found that are willing to participate and can have funding ready in case they are assigned to the experimental group. Secondly, the research team has to effectively collaborate with the local project coordinators of the day-care centres. Successful recruitment can very much depend on this collaboration as well as whether the local coordinator is able to motivate visitors of his/her day-care centre (and their informal caregivers) to participate in the trial. We will support the staff of day-care centres as much as possible in the process of recruitment, for example by written instructions for the local coordinator of the day-care centre regarding recruitment and motivating participants.

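### The subgroup aim is any difference in effect, or benefit versus none, but the only method named targets reversals of direction, so an empty tree would not show a uniform effect

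*Protocol article*

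**What the plan says.** The subgroup plan is the last paragraph of Effect evaluation, under Analysis of the data. It names one method and describes what that method delivers: "The method of QUalitative INteraction Trees (QUINT) [63] will be used for subgroup analysis. This allows for the identification of subgroups for whom the effect" is not the same. The possible moderators are given as examples ("for example differences related gender, age, ethnicity or severity of dementia"). It adds that cut-offs need not be set in advance, and that the result will support more specific advice "with regard to which type of participant or informal caregiver the intervention has a positive effect or not".

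The main analysis is in the same section: "we will use mixed model regression analysis which will take into account the effect of clustering" by centre, confounders and missing data. No treatment-by-moderator term is mentioned.

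On the expected direction, the Discussion states: "We expect that exergaming will have positive effects on people living with dementia in several domains". The Background reasons the same way. Neither section predicts a subgroup that would do better with regular activities.

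**The concern.** A qualitative interaction is one in which the sign of the treatment effect reverses: some people do better with exergaming, others with the comparator. A quantitative interaction is a difference in size without a reversal. The protocol describes its subgroup aim in terms that cover both, and the use it intends (a positive effect, or not) also covers benefit against no benefit. The method it names is aimed at the first kind only.

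Suppose exergaming helps people with milder dementia a lot and people with moderate dementia a little. The stated alternative, that the effect differs, is then true. A search for opposite-direction effects has nothing to find and may correctly return no tree. If that empty tree is taken to mean that the effect does not vary with gender, age, ethnicity or severity, the conclusion does not follow. The promised advice on who benefits would rest on an analysis that did not address the question.

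**Working it through.** **1. The plan's own figures.** The protocol gives no operating figure for the subgroup analysis. Its sample size, used below only to set the scale, reproduces:
- Inputs (Sample size calculation): difference 2, SD 4.6, power 80%, alpha 0.05 (two-sided assumed), ICC 0.05, 7 dyads per cluster, drop-out 4%.
- Total before clustering: 2 × 2 × (4.6 × (1.960 + 0.842) / 2)² = 166.1, against 166 stated.
- Design effect: 1 + (7 − 1) × 0.05 = 1.30, so 166 × 1.30 = 215.8.
- Drop-out: 215.8 / 0.96 = 224.8, or 215.8 × 1.04 = 224.4, against 224 stated.

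**2. Aim and method side by side.**

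| True pattern | Fits the stated aim? | A reversal of direction? |
|---|---|---|
| Everyone benefits, unequally | Yes (effect differs) | No |
| Some benefit, others do not | Yes (positive effect or not) | No |
| Some do better with regular activities | Yes | Yes |

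Only the third row is what a qualitative-interaction search targets. This step needs no numerical assumption.

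**3. Illustration with one fixed split.** Assumptions: N = 224, a 50/50 subgroup, 1:1 allocation, SD 1, so 224 / 4 = 56 per cell. The split is accepted if the observed effect is at least c in one half and at most −c in the other; c is assumed.
- Standard error of each subgroup effect: √(2/56) = 0.189; with a 1.3 variance inflation, √(2 × 1.3/56) = 0.2155.
- Standard error of the difference between subgroups: 0.189 × √2 = 0.267, or 0.305 inflated.
- Effects 0.8 v 0.2 SD, c = 0.20, no inflation: the smaller effect must fall to −0.20, with probability Φ((−0.20 − 0.20)/0.189) = Φ(−2.12) ≈ 1.7%. Interaction test: Φ(0.6/0.267 − 1.96) = Φ(0.285) ≈ 61%.
- Effects 0.87 v 0 SD, c = 0.20, no inflation: Φ(−0.20/0.189) = Φ(−1.06) ≈ 14.5%. Interaction test: Φ(0.87/0.267 − 1.96) ≈ 90%.

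Simulated results (20,000 runs), without / with the 1.3 inflation:

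| Effects (SD) | Split, c = 0.30 | Split, c = 0.20 | Interaction test, 0.05 |
|---|---|---|---|
| 0.8 v 0.2 | 0.5% / 1.0% | 1.8% / 3.2% | 62% / 51% |
| 0.87 v 0 | 5.7% / 8.4% | 14.5% / 18% | 90% / 82% |
| 0.435 v −0.435 | 58% / 55% | 80% / 75% | 90% / 82% |

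**4. Illustration with a search.** Assumptions: 224 × 0.96 = 215 participants, 24 centres, ICC 0.05, four candidate moderators, and true moderator severity, split at MMSE 17. The first split is sought over all cut-offs, with at least 10% of each arm per leaf, leaf effects of opposite sign, and a criterion combining effect size and leaf size. An assumed minimum leaf effect is then applied. There are 600 replicates per scenario. The comparator is a treatment-by-severity term with centre effects, tested at 0.05 and at 0.05/4 = 0.0125.

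| True effects (SD) | Severity flagged at minimum 0 / 0.1 / 0.2 / 0.3 SD | Interaction test, 0.05 / 0.0125 |
|---|---|---|
| 0.3 and 1.0 | 30 / 13 / 8 / 4% | 57 / 36% |
| 0 and 0.8 | 73 / 51 / 34 / 21% | 73 / 49% |
| −0.4 and 0.4 | 87 / 83 / 70 / 49% | 65 / 45% |
| No effect (any tree) | 95 / 68 / 37 / 10% | 4.5 / 0.8% |

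Same-direction differences are largely missed at every minimum from 0.1 to 0.3 SD. For benefit versus none, the answer depends heavily on the minimum. With no minimum the rule equals the 0.05 test (73%), but it also returns a tree in 95% of trials with no effect at all.

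**The case against.** Several points on the other side stand.

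- **Advice on whether to offer exergaming is close to QUINT's question.** For whom the effect is positive or not can be read as for whom to offer it. But the preceding sentence promises subgroups whose effect differs, and no benefit is still not a reversal.
- **Reversals are plausible.** A reader might infer that they are the least likely pattern because the Harms section rates the risk as negligible. That section concerns injury, not relative efficacy. Control activities include group gymnastics and walking, so some people could do better with them and come to no harm. The positive expectations in the Background and Discussion are general ones. QUINT is therefore worth keeping; in the reversal scenario it beats the interaction test at minima of 0 to 0.2 SD.
- **The numbers are soft.** A reader might infer that every ordinary difference is mostly missed. For 0 v 0.8 SD that depends on the minimum: 51% at 0.1 SD is level with the Bonferroni test (49%). The interaction test is also handed the true moderator, while the tree must search. The subgroup effects of 0.8 to 1.0 SD are assumed; the only design effect in the protocol is 2 / 4.6 = 0.43 SD. Neither illustration models full tree growing and pruning, and their percentages differ.
- **What a returned tree would mean cannot be checked here.** A reader might infer that any tree must label one leaf as worse off with exergaming, so that the advice is wrong either way. QUINT's acceptance and labelling rules are in a cited source that is not at hand, and the protocol does not say how an empty tree will be read. The supportable claim is that the result may mislead.
- **Further moderator models may sit in an analysis plan not shown.** Their absence alone would be no finding. The finding is that the article fixes a method and describes it as answering a wider question than it targets.

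**Conclusion.** The point holds as a mismatch between stated aim and named method in a secondary analysis. Same-direction differences would be largely missed (4 to 13% against 57%, or 36% after Bonferroni, for 0.3 v 1.0 SD). Benefit-versus-none patterns may be missed (21 to 51% against 73%, or 49%, for 0 v 0.8 SD). Both ranges assume a minimum leaf effect of 0.1 to 0.3 SD, which the protocol does not state, together with the assumed effects and first-split search above. Dropping the minimum is no remedy, given trees in 95% of null trials. The mismatch itself depends on none of these figures. An empty tree would not show that the effect is the same for everyone. The primary comparison is unaffected.

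**What to change.** 1. Add exploratory treatment-by-moderator interaction terms for gender, age, ethnicity and severity to the centre-level mixed model already planned. Keep moderators continuous where possible, and report each interaction estimate with its confidence interval.
2. Keep QUINT, described as a search for subgroups whose effects go in opposite directions.
3. Reword the subgroup paragraph in Effect evaluation accordingly, and state that an empty tree is not evidence of a uniform effect.

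The cost is wording and four exploratory terms, with no new data or participants. Two limits remain. Interaction terms need named moderators and do not supply cut-offs, which is a further reason to keep QUINT beside them. Power is only moderate, about 35 to 75% in the same-direction and benefit-versus-none search scenarios above, so the confidence intervals should carry the interpretation.
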